### Interventions

We translated the FC protocol for relatives of people with BPD into Spanish. It is one of the first programs designed to be applied directly to relatives of patients with BPD. The program is an adaptation of different Dialectical Behavior Therapy strategies, one of the most researched and empirically supported treatments for BPD people [24, 38]. It is composed of six modules divided into 12 sessions lasting approximately 2 h each. The intervention protocol is structured in a caregiver handbook [25]. In the following section, the modules in each treatment program are briefly described.

The FC protocol includes components aimed primarily at reducing distress and burden and improving overall family functioning: relationship mindfulness skills, family environment skills, validation skills, and problem management skills. Furthermore, the program includes Psychoeducation about borderline personality disorder.

#### Family connections (FC)

This intervention program consists of six modules with two sessions each, designed to improve family attitudes and reduce family exhaustion. Each module has specific objectives and practical exercises, as well as videos with examples of people suffering from BPD and their relatives:
*Introduction*. The objective of this module is to provide information about the aims of the program, weekly format and guidelines, statement of rights, and criteria and symptoms of BPD. The central role of emotion regulation is also presented.*Family Education*. The purpose of this module is to present treatment programs for BPD and comorbid disorders, biosocial factors related to the etiology of the disorder, the difficulties BPD provokes in the family members, and the need for help. It also shows the transactional model of the development of BPD and related disorders.*Relationship Mindfulness Skills*. This module aims to define a validating family environment, being mindful of the relationship, emotion regulation skills, and states of mind.*Family Environment Skills*. The aim is to understand the relationship between the individual and the family’s welfare, the importance of maladaptive ways of thinking related to blame, and the concept of radical acceptance.*Validation Skills*. The objective of this module is to understand what validation means and learn validation and self-validation skills. Moreover, in this module, the relatives learn how to set clear limits and achieve self-respect.*Problem Management Skills*. This module focuses on interpersonal efficacy, defining problems and solutions, and problem management skills.

### Adaptation to Spanish

The FC program has been translated into Spanish by the Puerto Rican research group directed by [name], and adapted to the Spanish spoken in Spain by our research team. This translation was performed by clinical experts who were familiar with both DBT [39, 40] and the FC program. The translation included the FC program manual, as well as the videos that accompany the program (they were subtitled in Spanish) and the brochures, leaflets, and handouts.

#### Treatment as usual (TAU)

Treatment as usual is the program routinely offered to BPD patients’ relatives in the clinical centers participating in this trial. The intervention includes 12 therapeutic sessions in six modules. Each module has specific objectives and practical exercises.
*Introduction*. This module consists of an overview of the treatment and the aims of the group. Furthermore, it focuses on the definition of personality disorders, BPD and its clinical characteristics, the role of emotion regulation, and comorbid disorders.*Family Education*. The aim of this module is to explain the diagnostic criteria for BPD, associated problems (alcohol and substance use and eating disorders), the DBT model, and the main goals of the treatment.Validation Skills. The purpose of this module is to explain what validating and invalidating environments are, the consequences of an invalidating environment, and how to use validating skills.*Crisis Management Skills*. This module aims to prevent crises by explaining how to manage anger and learning how to act in the presence of self-injuring and suicidal behaviors. Moreover, acceptance skills are shown in this module.*Problem Management Skills*. This module helps the relative to know how to deal with problems and set clear limits, handle conflict in everyday situations, confront unacceptable behavior, and manage emotionally charged conversations.*Relapse Prevention*. It aims to strengthen the strategies learned throughout the program, schedule future practice, and teach the participants how to identify and cope with future high-risk situations.

### Measures

Table 1 presents a summary of the measures.

### Caregiver measures (participants)

#### Sociodemographic interview

Demographic variables questionnaire: age, family constellation, sex, educational level, income, marital status, number / age of children, and psychiatric history.

### Primary outcomes

#### Burden assessment scale (BAS) [41]

It consists of 19 items that assess the caregivers’ objective and subjective burden in the past 6 months. Items are rated on a 4-point Likert scale ranging from 1 to 4, and higher values indicate a heavier burden. Internal reliability of the scale ranges from .89 to .91, and it shows adequate validity [42]. This scale is not validated in Spanish and it will be an objective of this work.

#### Family assessment device – global functioning scale (FAD-GFS) [43]

It is a self-report questionnaire consisting of 60 items related to family functioning. It is composed of seven subscales: Problem-Solving, Communication, Roles, Affective Responsiveness, Affective Involvement, Behavior Control, and General Functioning. Cronbach’s alphas range from .72 to .83 for the subscales, and.92 for general functioning, and test-retest reliabilities for the FAD scales were adequate [44]. This scale is not validated in Spanish and it will be an objective of this work.

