**Methods:**

The study is a randomized controlled trial. The participants will be recruited in a Personality Disorders Unit and randomly assigned to one of two treatment conditions: *Family Connections group (FC)* or Treatment As Usual (TAU). Primary outcome measures will be the BAS and FAD-GFS. Secondary outcomes will include DASS-21, FES, GS, and QLI. Participants’ treatment acceptance and degree of satisfaction will also be measured. Participants will be assessed at pre-, post-treatment, and 6-month follow-up. Intention to treat and per protocol analyses will be performed.

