### Study population, recruitment, and eligibility criteria

The sample will consist of relatives of people with BPD. Recruitment will be carried out among relatives of patients treated at clinical centers specializing in the treatment of BPD in the Valencian region. Inclusion criteria will include the following: a) being 18 years old or more; b) having a family member diagnosed with BPD; c) ability to understand and read Spanish; and d) providing written informed consent. Participants will be recruited by clinicians working in these clinical centers in three Spanish cities (Castellón, Valencia, and Alicante), until the required sample is complete. Clinicians will offer patients’ families the opportunity to participate in the study and, after explaining it, obtain their informed consent. All the psychologists who participate in this research will have at least a master’s degree in Clinical Psychology and specialized FC training.

A psychologist will contact the participant to determine his/her inclusion in the study. At that time, the researcher will collect the baseline data and determine whether the inclusion criteria are met (see Table 1). Then the psychologist will contact a person outside the research group who will perform the individual randomization and inform the assessor of a code that corresponds to the type of treatment. This psychologist will be unaware of the characteristics of the study.

**Table 1 Tab1:** Study measures and evaluation times

Participant	Measure	Aim	Evaluation time
Caregiver	S-D Interview	Diagnosis	BL
	BAS	Severity of burden symptoms	BL, Post-T and FU
	FAD-GFS	Familiar Global Functioning	BL, Post-T and FU
	DASS-21	Depression, anxiety and stress symptoms	BL, Post-T and FU
	FES	Family empowerment	BL, Post-T and FU
	QLI-Sp	Quality of life	BL, Post-T and FU
	OTSM	Treatment opinion and acceptance	PM
Patient	FAD-GFS	Familiar Global Functioning	BL, Post-T and FU
	DASS-21	Depression, anxiety and stress symptoms	BL, Post-T and FU
	DERS	Difficulties in emotional regulation	BL, Post-T and FU
	LEAP	Emotional availability of parents	BL, Post-T and FU
	VIRS	Validating and invalidating responses	BL, Post-T and FU

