### Data analyses

In order to analyze whether there are differences between the experimental conditions before the application of the treatment, Student’s t tests will be performed for the continuous variables, and chi-square tests for the categorical variables. To compare the effectiveness of the two treatment conditions, we will perform a multivariate analysis of variance for repeated measures (MANOVA) for the variables with subscales, and ANOVA for the single variables, taking the pretreatment, posttreatment and follow-up moments as within-subject factor and the treatment condition (FC vs TAU) as between-subject factor.

Moreover, between-group changes will be computed by calculating standardized effect sizes (Cohen’s d). Finally, we will perform zero-order correlations and linear regression analyses between the measures of the caregivers and the measures of the patients.

Because the trial is still going on, the state of the art in analytic methodology for RCT will be reviewed before analyzing the data, and so variations in the selection of the most appropriate analytic procedures may occur.

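### The primary outcome FAD-GFS is named as one global score but described as a seven-subscale instrument, so the analysis rule leads to either an ANOVA or a non-directional MANOVA

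*Protocol article*

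**What the plan says.** **Status of the outcome.** The Methods part of the abstract states: "Primary outcome measures will be the BAS and FAD-GFS".

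**Name and aim.** The measure is headed as a global functioning scale, and Table 1 gives its aim as "Familiar Global Functioning". Both point to one construct.

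**Description.** The entry under that heading reads "It is a self-report questionnaire consisting of 60 items related to family functioning" and continues: "It is composed of seven subscales: Problem-Solving, Communication, Roles, Affective Responsiveness, Affective Involvement, Behavior Control, and General Functioning". It reports reliability separately for the subscales (.72 to .83) and for general functioning (.92).

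**Analysis rule.** The Data analyses section prescribes "MANOVA) for the variables with subscales, and ANOVA for the single variables", with the three time points as the within-subject factor and FC versus TAU as the between-subject factor. It adds Cohen's d for between-group change and says that the choice of procedures may be revised before analysis.

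**Hypotheses.** At the end of the Background, hypothesis (a) expects overall family functioning to improve. Hypothesis (b) expects FC to do better than TAU on family functioning, among other measures.

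**The concern.** The article never says which FAD score is the primary variable, and its own rule makes the choice of test depend on that. Two analysts who both follow the document could report different primary results: one an ANOVA on a single score, the other a MANOVA on seven.

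The second route is the literal one, because the entry lists subscales, and it fits the hypotheses poorly. A multivariate group-by-time test asks whether the arms differ in any way on the vector of seven subscales. One subscale could drive a significant result, and so could some subscales improving while others worsen. Either could then be reported as FC improving family functioning, although the test carries no direction and gives no single FC-TAU difference in overall functioning. This affects one of only two primary outcomes.

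**Working it through.** **Step 1. Set the statements side by side.**

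| Place in the protocol article | What it implies for the FAD | Test under the Data analyses rule |
|---|---|---|
| Heading of the measure, abbreviation lists, abstract | one global score | ANOVA |
| Table 1, aim | one construct | ANOVA |
| Text of the measure entry | 60 items, seven subscales | MANOVA |
| Hypotheses (a) and (b) | overall functioning; FC better than TAU | a directional question about one quantity |

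Three of the four point to a single score. The text of the entry, which is what triggers the subscale rule, does not.

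**Step 2. Reproduce the plan's own sample size.** Inputs from the Sample size section: d = 0.60 (stated for burden), two-sided alpha 0.05, power 0.80, t test. For n per arm, the noncentrality is d × √(n/2) on 2n − 2 degrees of freedom.
- n = 45: 0.60 × √22.5 = 2.846, df 88, power 0.804.
- n = 44: power 0.795.

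The stated 45 per arm reproduces. If 29% of the planned 58 per arm are lost, 58 × 0.71 = 41.2 remain. At 41 per arm the power is 0.765.

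**Step 3. Power of a seven-variable test of the same contrast.** For two arms and p = 7 variables I use Hotelling's T² as a noncentral F with 7 and 2n − 8 degrees of freedom and noncentrality (n/2) × D². Here D² is the squared Mahalanobis distance between the arms. At n = 45 the degrees of freedom are 7 and 82, and the critical value is 2.12.

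The documents give neither subscale effects nor correlations, so these are assumptions:
- General Functioning differs by d = 0.60, borrowed from burden.
- All pairs of subscales share one correlation ρ.
- Participants are independent.

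*Floor.* D² cannot be smaller than the squared effect on General Functioning, 0.60² = 0.36. The noncentrality is then 22.5 × 0.36 = 8.1.

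*All seven subscales at 0.60.* D² = 7 × 0.36 / (1 + 6ρ).

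*Effect on General Functioning, a common effect on the other six.* D² = δ′R⁻¹δ, with R the exchangeable correlation matrix.

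| Assumed scenario | D² | Power, 45 per arm | Power, 41 per arm |
|---|---|---|---|
| Floor | 0.360 | 0.47 | 0.42 |
| All seven 0.60, ρ = 0.9 | 0.394 | 0.51 | 0.46 |
| All seven 0.60, ρ = 0.7 | 0.485 | 0.62 | 0.56 |
| All seven 0.60, ρ = 0.6 | 0.548 | 0.68 | 0.63 |
| All seven 0.60, ρ = 0.5 | 0.630 | 0.75 | 0.70 |
| All seven 0.60, ρ = 0.4 | 0.741 | 0.83 | 0.78 |
| All seven 0.60, ρ = 0.3 | 0.900 | 0.91 | 0.87 |
| Other six 0.30, ρ = 0.6 | 0.372 | 0.48 | 0.44 |
| Other six 0, ρ = 0.6 | 0.783 | 0.85 | 0.81 |
| Other six 0, ρ = 0.7 | 1.038 | 0.95 | 0.92 |
| *Single General Functioning score* | – | *0.80* | *0.77* |

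At 45 per arm the seven-variable test reaches 0.80 once D² is about 0.69 or more. At the floor it would need 84 per arm. All figures are for one between-arm contrast, not for the planned model with three time points.

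**The case against.** **The MANOVA is not certain.** The name, the abbreviation lists and Table 1 all support one score, which the rule sends to ANOVA. The entry may simply describe the parent instrument, as the DASS-21 entry does when it opens with the 42-item form. This stands. A reader might infer that the protocol commits family functioning to a MANOVA, but it does not say so. What remains is that the article supports both readings and states nothing that chooses between them.

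**Low power is not shown.** A reader might also infer that the omnibus test is bound to be weak. The documents do not support that. Power is lower than for a single score in many of the scenarios above, but higher when the subscales are weakly correlated with equal effects, or when the effect is confined to General Functioning and the correlations are high. The 0.60 is stated for burden, not for the FAD. The argument about direction needs none of these assumptions.

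**Effect sizes are planned as well.** Cohen's d has a direction, and univariate follow-up to a MANOVA is a detail that an article may leave to a fuller plan. This stands in part. The article does not say which FAD score the effect size is for, so the primary variable is still undefined. The statement that procedures may be reviewed before analysis does not define it either.

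**The same problem might be read into the BAS.** Its entry mentions objective and subjective burden but lists no subscales, so the text does not show the same conflict there.

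**Conclusion.** The point holds as a conflict over which FAD score is primary, with a consequence for the test. The name and Table 1 describe one global measure, the entry describes seven subscales, and the analysis rule turns that difference into two different primary analyses. The literal one is a non-directional omnibus test that does not by itself answer the hypothesis about overall family functioning. This conclusion rests on the text alone.

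The effect on power is conditional. Against 0.80 for a single score, the seven-variable test has between 0.47 (the floor) and above 0.90 at 45 per arm. That range rests on d = 0.60 carried over from burden, on assumed subscale effects and correlations, on independent participants (although relatives of the same patient are randomised together) and on one contrast in place of the repeated-measures model. It should be corrected before analysis, but it does not undermine the trial.

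**What to change.** 1. In the FAD-GFS entry, state that the primary family-functioning outcome is the General Functioning subscale score. Describe the 60-item, seven-subscale form as the instrument from which that score is taken.
2. In Data analyses, exempt this outcome from the subscale rule. Analyse it as a single variable and report its FC-TAU difference with a confidence interval at a named time point.
3. List the other six FAD subscales as secondary outcomes.

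The cost is wording only. The 60-item form already yields the score, so data collection does not change. The Data Availability statement places the trial at the recruitment stage, so the definition can be fixed before the data are analysed.

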### Secondary outcomes

#### Depression, anxiety and stress scale (DASS-21) [45]

This scale has 42 items about negative emotional symptoms. They proposed a short version with 21 items. The DASS-21 showed good factor structures. Regarding the internal consistency, Cronbach’s alphas were excellent for the DASS-21 subscales: Depression (α = .94), Anxiety (α = .87), and Stress (α = .91) [46]. We used the Spanish version validated by Daza, Novy, Stanley and Averill [47].

#### Family empowerment scale (FES) [48]

It consists of 34 items divided into three subscales: family, service system, and involvement in community, which refer to three forms of empowerment: attitudes, knowledge, and behaviors. Items are rated on a scale from 1 to 5, and higher scores indicate a greater sense of empowerment. The psychometric properties are the following: regarding the internal consistency of the FES subscales, the coefficients ranged from .87 to .88, and validity and reliability were adequate. This scale is not validated in Spanish and it will be an objective of this work.

#### Quality of life index-Spanish version (QLI-Sp) [49]

This index consists of 10 items that assess perceived quality of life, including physical and emotional well-being, self-care and independent functioning, occupational and interpersonal functioning, social-emotional and community support, personal and spiritual fulfillment, and a global perception of quality of life. Higher scores indicate higher quality of life. This instrument has good psychometric properties, with a Cronbach’s alpha of .89 and high test–retest reliability (*r* = 0.87).

#### Opinion of treatment scale by modules (OTSM)

The Opinion of Treatment Scale by Modules is an instrument developed by our research team and adapted from Borkovec and Nau [50]. It is designed to assess the participants’ opinion and acceptance of the program. Furthermore, it evaluates the level of change obtained with regard to the therapeutic modules. Questions involve how logical the treatment seemed, degree of satisfaction, if they would recommend the program, if they think this program would be useful to treat their problems or others, and expectations about the program. It evaluates the six treatment modules in the two conditions. There are two subscales: one evaluates the learning of the skills taught in the module and is rated from 0 (not at all) to 10 (a lot), and the other evaluates how the module has helped the caregiver to improve several aspects, such as knowing and understanding the problem, understanding emotions, mindfulness of the relationship with their relative, acceptance, family atmosphere, and problem solving, and it is rated from 1 (not at all) to 4 (a lot). Additionally, there is an expectation question only at the end of the first module, where the participants answer the question: “In general, what expectations do you have about the program?”

### Patient measures

#### Sociodemographic interview

***Family Assessment Device – Global Functioning Scale (FAD-GFS)*** [43].

***Depression, Anxiety and Stress Scale (DASS-21)*** [45].

#### Difficulties in emotion regulation scale – Spanish version (DERS) [51]

The authors adapted the scale to spanish and they reduced the items from 36 to 28 with five subscales: emotional lack of control, life interference, lack of emotional attention, emotional confusion, and emotional rejection. All the items have a Likert type design, with a score between 1 and 5, where 1 means “Hardly Ever” and 4 “Usually”, where higher score means more difficulties. Internal consistency was excellent (α = .93) and good test-retest reliability (pl = .74, *p* < .001).

#### Lum emotional availability of parents (LEAP) [52]

It consists of 15 items that measure mothers’ and fathers’ emotional availability perceived by the patient. Items are rated on a 6-point Likert scale ranging from 1 (never) to 6 (always). Internal consistency was excellent in a non-clinical sample for the mother form (α = .96) and the father form (α = .97); and in a clinical sample, for the mother form (α = .92) and the father form (α = .93). This instrument has adequate test–retest reliability for the mother form (*r* = .92) and the father form (*r* = .85). This scale is not validated in Spanish and it will be an objective of this work.

#### Validating and invalidating responses scale (VIRS) [53]

The Validating and Invalidating Responses Scale is a 16-item self-report that evaluates levels of validation and invalidation of caregivers’ responses. This instrument has two subscales: validation and invalidation responses. These two subscales are moderately correlated. Items are rated on a 5-point Likert scale, ranging from 0 (never) to 4 (almost all the time), and higher scores indicate more perceived validation or invalidation from the caregiver who is assessed. There are no psychometric properties available on the VIRS yet. This scale is not validated in Spanish and it will be an objective of this work.

Study measures and evaluation times are summarized in Table 1.

### Data analyses

In order to analyze whether there are differences between the experimental conditions before the application of the treatment, Student’s t tests will be performed for the continuous variables, and chi-square tests for the categorical variables. To compare the effectiveness of the two treatment conditions, we will perform a multivariate analysis of variance for repeated measures (MANOVA) for the variables with subscales, and ANOVA for the single variables, taking the pretreatment, posttreatment and follow-up moments as within-subject factor and the treatment condition (FC vs TAU) as between-subject factor.

Moreover, between-group changes will be computed by calculating standardized effect sizes (Cohen’s d). Finally, we will perform zero-order correlations and linear regression analyses between the measures of the caregivers and the measures of the patients.

Because the trial is still going on, the state of the art in analytic methodology for RCT will be reviewed before analyzing the data, and so variations in the selection of the most appropriate analytic procedures may occur.

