### Sample size

To determine the sample size, the effect sizes found in the literature on the subject have been considered. The controlled study by Grenyer et al. [35], which tested a group psychoeducation protocol for caregivers of people with BPD, reported medium to large effect sizes (dyadic adjustment, *d* = .78; family empowerment, *d* = 1.4). In addition, on measures of burden, Grenyer [35] reported significant improvements between post assessment and the 12-month follow-up, with medium effect sizes (Burden Assessment Scale, *d* = .45). These effects are consistent with the literature on psychological treatments for other psychiatric disorders, such as the meta-analysis of psychological interventions for caregivers of people with bipolar disorders (Burden, *g* = −.80) [36].

Taking these data into account, in the present study, adopting a conservative approach, an effect size of 0.60 is expected because our design includes two experimental conditions. Considering an alpha of 0.05 and a statistical power of 0.80 on a 2-tailed *t* test, the total sample size needed to reach an effect size of 0.60 for burden is 90 participants (45 participants per experimental condition). To control the maximum possible loss of participants during treatment, based on the literature about programs for family members of patients with BPD, a 29% dropout rate is expected [20, 23–25, 27]. Thus, the required sample size should be a total of 116 participants (58 participants per group). These calculations were made with the software program G*Power 3.1 [37].

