However, this study has some limitations. We do not expect to have recruitment difficulties because our research team collaborates with different clinical centers, but even so we would have liked to increase the number of centers participating in the study. This was not possible for funding and logistic reasons. Another limitation is that we included a follow-up at 6 months. We would have liked to carry out a long-term follow-up, but due to the conditions of the centers, it is difficult to contact relatives or patients who leave treatment or are discharged.

Finally, the aim of this study is to contribute to the literature on the efficacy of the FC program for relatives of people with BPD. We hope that this study contributes to the exploration of the efficacy and acceptability of programs designed to improve global family functioning and reduce family members’ burden. It will also contribute to improving our understanding of the relationships that may exist between the clinical evolution of the family members receiving the program and the evolution of the patients. If significant results are achieved, there will be an effect on the design and application of future family intervention programs, as a way to improve the overall functioning of the family climate and reduce the burden and distress they face. Finally, this study will allow the possible application of the program to Spanish-speaking populations in other countries.

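### The only stated between-arm model, a three-occasion repeated-measures ANOVA/MANOVA, drops relatives with a missed assessment, so by itself it does not deliver the promised intention-to-treat analysis

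*Protocol article*

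**What the plan says.** The Data analyses section of the protocol article gives one model for comparing the arms: repeated-measures MANOVA for measures with subscales and repeated-measures ANOVA for single scores, "taking the pretreatment, posttreatment and follow-up moments as within-subject factor", with FC versus TAU between subjects. Standardised effect sizes accompany it.

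The Methods paragraph of the abstract states: "Intention to treat and per protocol analyses will be performed". The Data analyses section mentions neither analysis set. It also does not say how a relative with a missed assessment enters the model. It closes by reserving the right to change procedures after a review of current methods.

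The Sample size section says that "a 29% dropout rate is expected". It introduces this allowance with the words "To control the maximum possible loss of participants during treatment" and uses it to raise 90 participants to 116.

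**The concern.** Classical repeated-measures ANOVA and MANOVA need a complete set of occasions for each person, so a relative who misses one of the three is removed altogether. With substantial dropout expected, the analysed set is then the relatives with complete data rather than everyone randomised, which is not what intention to treat means.

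Three things are at stake:

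- **Data:** the observed baseline and post-treatment scores of a relative who misses only the 6-month visit are thrown away.
- **Precision:** fewer relatives are analysed than the sample-size calculation assumed.
- **Validity:** the comparison loses the protection of randomisation if the reasons for missing an assessment differ between arms.

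**Working it through.** **Inputs, all from the Sample size section:** two-sided t test, alpha 0.05, power 0.80, effect size d = 0.60, 45 per arm (90 in total), 29% dropout, 116 randomised (58 per arm). By the Study population section, baseline data are collected before randomisation, so every randomised relative should have a baseline score.

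**Step 1. Reproduce the plan's figures.** Power comes from the noncentral t distribution with noncentrality d / √(2/n) and 2n − 2 degrees of freedom.

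- n = 45: 0.60 / √(2/45) = 2.85, power 0.804.
- n = 44: power 0.795.

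So 45 per arm, 90 in total, is reproduced. The 116 is reproduced as 90 × 1.29 = 116.1.

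**Step 2. Relatives kept by a complete-case analysis, if 29% means lost assessments.**

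- Excluded: 116 × 0.29 = 33.6, about 34.
- Analysed: 116 × 0.71 = 82.4, about 82. Per arm: 58 × 0.71 = 41.2, about 41.

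**Step 3. Power with those relatives.** n = 41: 0.60 / √(2/41) = 2.72, power 0.765 (0.775 by the normal approximation).

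| Loss of assessments | Analysed per arm | Power at d = 0.60 |
|---|---|---|
| none | 58 | 0.893 |
| 22.4% (1 − 90/116) | 45 | 0.804 |
| 29% | 41 | 0.765 |

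This is power for the t test on which the trial was sized. Power for the group-by-time test depends on correlations between occasions, which the article does not give. The 29% is loss during treatment. Any further loss before 6 months would lower the 82, but the article gives no figure for it.

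Part of the shortfall comes from multiplying by 1.29 rather than dividing by 0.71 (90 / 0.71 = 126.8, so 127). That is a separate point.

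**Step 4. Can the estimate shift?** The article has no figures for this, so the following is an illustration under assumed values: SD 1 at each occasion; correlation 0.6 between adjacent occasions and 0.5 between baseline and follow-up; true effect −0.60 (lower burden under FC); 29% missing in each arm; log-odds slope of 1 per SD of the score that drives dropout. The last column is the between-arm difference in change to follow-up among completers.

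| Dropout mechanism | Estimate |
|---|---|
| Random in both arms | −0.60 |
| Higher baseline burden leaves, both arms | −0.60 |
| Higher baseline burden leaves, TAU only | −0.73 |
| Higher baseline burden leaves, FC only | −0.48 |
| Higher leaves in TAU, lower leaves in FC | −0.85 |
| Lower leaves in TAU, higher leaves in FC | −0.36 |

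When dropout was made to depend on the post-treatment score instead, in one arm or in both, the estimate stayed at −0.60 under these correlations. Bias therefore needs a mechanism that differs between arms, and even then it is not automatic. It can go in either direction.

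**The case against.** The strongest reply is that the Data analyses section names a test and is silent on missing values. Imputing first and then running the same ANOVA would satisfy both that section and the abstract. The article is condensed, and a full analysis plan may say exactly this. That stands in part: the stated model does not make intention to treat impossible. But the point is more than an omitted detail. The article fixes a model which, at its own expected dropout, does not by itself give the analysis set it promises. The closing reservation about changing methods commits to nothing.

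The figure of 34 excluded is also conditional. The 29% is presented as a maximum loss during treatment, and relatives who stop sessions but still return questionnaires stay in the model. This stands. Against it, the Sample size section itself treats dropout as loss from the analysed sample.

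Three stronger readings are tempting, and the document does not support them.

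- **Who will be missing.** A reader might infer this from the Discussion, which says "it is difficult to contact relatives or patients who leave treatment or are discharged". That sentence explains why there is no follow-up beyond 6 months, and it also covers patients and people who are discharged. It does not say who will miss the post-treatment or 6-month assessment.
- **A definite bias.** A reader might put one number on it by assuming a gap between dropouts and completers in one arm. The article gives no such gap. Both arms have 12 sessions in six modules, and no differential dropout is predicted. The hypothesis that FC will be rated higher makes differential retention plausible, no more.
- **Merged analysis sets.** A reader might infer that the intention-to-treat and per-protocol sets would become nearly the same. Per protocol is not defined here and could depend on attendance, so this cannot be shown.

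**Conclusion.** The point holds. Without imputation, which is not named, the only stated between-arm model is a complete-case analysis, and this is at odds with the intention-to-treat promise in the abstract.

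If the 29% dropout means lost assessments, about 34 of 116 relatives are excluded and about 82 are analysed. Power is then about 0.77 at d = 0.60 instead of 0.80. If relatives who leave treatment still complete their assessments, the loss is smaller. Bias is possible, of unknown size and direction, and arises only if dropout is related to burden differently in the two arms.

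Because this concerns the primary comparison, it should be settled before the data are analysed.

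**What to change.** In the Data analyses section, make the primary analysis a likelihood-based linear mixed model for repeated measures with arm, time and arm-by-time. Include all randomised relatives in their assigned arm and use every available assessment. Add a random effect for family, because the Study design section randomises relatives of one patient together. Multiple imputation before the planned ANOVA/MANOVA is an acceptable alternative if the authors prefer to keep that model.

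Add one sensitivity analysis for data not missing at random, for example delta-adjusted imputation. Keep the complete-case ANOVA and label it supportive.

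The cost is slightly more analysis work. The change keeps all relatives in the model and is valid when missingness depends on observed scores. It should not be expected to restore power of 0.80 by itself, because a relative with only a baseline score adds little to the later contrasts.
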